#### Secondary

Secondary outcomes will be:
the proportion of women delivered with preterm pre-eclampsia out of all deliveries for pre-eclampsia;prolongation of pregnancy,proportion of women delivered < 34 weeks’ gestation with pre-eclampsia/total deliveries < 34 weeks’ gestation.

Additional maternal outcomes including
maternal mortality (death in pregnancy or within 42 days of delivery)severe hypertension (systolic BP ≥ 160 mmHg or diastolic BP ≥ 110 mm/Hg),HELLP syndrome,pulmonary edema,eclampsia,stroke,coma,renal or hepatic dysfunction or thrombocytopenia;length of maternal hospital stay

Additional perinatal outcomes will include
fetal death > 20 weeks’ gestation,perinatal death (stillbirth after 27^+ 6^ weeks or early neonatal death < 7 days of birth);Apgar score < 3 at 5 min,respiratory distress syndrome,necrotizing enterocolitis,confirmed sepsis,non-lethal seizures or coma,small for gestational age infants (< 10th and 3rd WHO centile),length of neonatal hospital stay.

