### Data safety and monitoring committee (DMC)

Monitoring of the accuracy and adequacy of data collection will be the responsibility of the Data Manager. He/she will investigate and wherever possible correct implausible entries and missing fields as they occur. Systematic problems will be referred to the Management Committee. A Data Monitoring Committee that will meet every four months will review the progress of the trial in terms of outcomes and results.

All responsible researchers by each centre have been instructed to report specific and important adverse outcomes involved with women participating in the trial. These specific adverse outcomes are: maternal death, fetal or neonatal death, eclampsia, HELLP syndrome, stroke and pulmonary edema requiring ventilation.

Rules for stopping the trial: It is possible for the intervention to result in inappropriate prolongation of pregnancy and serious events leading to adverse maternal or foetal/neonatal outcomes. The DMC will use the Haybittle-Peto rule, and stop the intervention if the *p*-value of the interim analysis is less than *P* < 0.001, and carry out a full interim analysis adjusting for baseline.

If these committees determine that this intervention is being used appropriately and increases adverse outcomes, then the trial will be stopped.

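### The seizure/coma outcome counts only non-lethal cases, so fatal cases drop out of it, and those dying on day 7 or later are missed by the perinatal death outcome as well

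*Protocol article*

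**What the plan says.** The Secondary subsection of Outcome measures lists the perinatal outcomes as separate items. One is "non-lethal seizures or coma". Two are mortality outcomes: "fetal death > 20 weeks" of gestation, and perinatal death, which combines stillbirth beyond 27+6 weeks with "early neonatal death < 7 days of birth". No secondary outcome names a neonatal death on day 7 or later.

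The section on the data safety and monitoring committee asks centres to report "maternal death, fetal or neonatal death, eclampsia, HELLP syndrome, stroke and pulmonary edema requiring ventilation". It puts no day limit on the neonatal deaths. It also states the risk directly: "It is possible for the intervention to result in inappropriate prolongation of pregnancy and serious events" that harm the mother, the fetus or the newborn.

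The Data analysis section gives each secondary outcome a model similar to that of the primary, with a suitable link function. The first aim of the trial includes better neonatal outcome.

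**The concern.** A morbidity item limited to survivors of the event depends on who survives. If the intervention can change survival, the item is no longer a clean measure of how often the morbidity occurs. That is a real possibility here. The intervention recommends deferral for women classed as low risk, and the article names fetal and neonatal harm from prolongation as a risk to be monitored.

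What is at stake is the neonatal part of the first aim. Among severe neurological events, the worst cases leave the numerator because they are the worst. The perinatal death outcome recovers those who die before day 7 but not those who die later. In a preterm population, later deaths are plausible.

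**Working it through.** The article gives no rate of neonatal seizures, coma or death, so there is no figure of its own to reproduce. The check has two parts.

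**1. Follow one liveborn infant through the stated definitions.** I read the restriction as covering coma as well as seizures. The grammar would also allow it to cover seizures alone.

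| Course of a liveborn infant | Seizure/coma item | Perinatal death | Safety report |
|---|---|---|---|
| Seizures, survives | counted | no | no |
| Seizures, dies before day 7 | not counted | counted | counted |
| Seizures, dies on day 7 or later | not counted | not counted | counted, as a neonatal death |
| No seizures, dies on day 7 or later | no | not counted | counted, as a neonatal death |

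The third row is the gap: an infant with both seizures and death enters neither the seizure outcome nor a mortality outcome. The fourth row shows that late deaths lack a secondary outcome even without seizures.

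**2. Size of the distortion, under assumed rates.** Let q be the share of infants with seizures or coma and f the share of those who die.

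- Listed rate = q × (1 − f)
- Rate of fatal cases = q × f
- Rate with the restriction removed = q

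With q = 5% in both phases:

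- f = 20%: listed 0.05 × 0.80 = 4.0%; fatal 0.05 × 0.20 = 1.0%
- f = 40%: listed 0.05 × 0.60 = 3.0%; fatal 0.05 × 0.40 = 2.0%
- f = 60%: listed 0.05 × 0.40 = 2.0%; fatal 0.05 × 0.60 = 3.0%

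With q = 10%, the listed rate is 8.0%, 6.0% and 4.0% for the same three values of f.

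When f goes from 20% to 40%, the listed outcome improves by a quarter (1.0/4.0) while fatal cases double. With the restriction removed, the rate stays at 5% (or 10%), so no false improvement appears.

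How much of the rise in deaths shows up in perinatal death depends on timing. Let g be the share of the fatal cases dying on day 7 or later, taken as equal in both phases. At q = 5%, perinatal death picks up (1 − g) × 1.0 percentage point of the increase. That is the full point if all die before day 7 and nothing if all die later.

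**The case against.** The strongest reply is that deaths are not hidden. Fetal death and perinatal death stand in the same list, and fetal or neonatal death is reportable to a committee that meets every four months under a stopping rule. On this view, non-lethal simply keeps morbidity apart from the death outcomes beside it. Much of this stands: an excess of fetal or early neonatal deaths would be seen, and a phase with more such deaths could look better only on this one item read alone. It does not cover deaths from day 7. Nor does a separate mortality row correct a morbidity rate that falls because more cases were fatal.

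A reader might go further and infer that other outcomes reward death too. An early death could shorten "length of neonatal hospital stay", and a later fetal death could lengthen "prolongation of pregnancy". For example, if survivors stay 20 days and infants who die stay 3, a rise in deaths from 5% to 10% lowers mean stay from 0.95 × 20 + 0.05 × 3 = 19.15 days to 0.90 × 20 + 0.10 × 3 = 18.30 days. But this holds only if deaths enter at their observed stay. The article states no rule on death for either outcome, and a condensed article may leave that to the full protocol or analysis plan.

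The inference also fails for respiratory distress, enterocolitis and sepsis. They carry no survivor restriction, so a liveborn infant who has one of them and then dies still counts.

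**Conclusion.** The point holds for one item and one gap. As written, the seizure/coma outcome excludes fatal cases. Those who die on day 7 or later are also outside perinatal death and are left to safety reporting. This is stated wording, so an analysis plan could not repair it without changing the definition.

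The size cannot be taken from the article. Under the assumptions above (affected share 5% to 10% and equal in both phases, lethal share rising from 20% to 40%), the false improvement is 1.0 to 2.0 percentage points. If the lethal share does not differ between phases, there is no distortion of the comparison, only an undercount. The primary outcome and the sample size are not affected. The documents do not support a wider claim that the secondary outcomes as a set favour the phase with more deaths.

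**What to change.** Delete the word non-lethal, so that seizures or coma in a liveborn infant count whether or not the infant survives. Report neonatal deaths from day 7 as a row beside perinatal death in the efficacy tables, and state the last day of that window, since the safety list gives none.

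The cost is small. Neonatal deaths are already reportable, so the change is a phrase in the outcome list and one further result. The downside is that an infant may be counted under both seizures and death, which a footnote can state. Composites of death with morbidity, or ranking death as the worst value, are not needed for this. They involve trade-offs of their own.

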### Knowledge transfer program

The activities for the Knowledge transfer (KT) program will be established in phases and constitute a strategy to improve commitment with recruitment and adherence to the study protocol.

Phase 1: the KT will address the problem of unnecessary delivery of women with preterm PE, its impact on fetal outcome and its magnitude in Brazil. The scale of and evidence for the problem will be presented to healthcare providers together with the proposed solution and its supporting information.

Phase 2: several strategies will be used of which the key component is the e-learning module [25]. One module will present the problem and supporting data and a second will outline the solution through the use of sFlt-1/PlGF and full-PIERS to grade the risks of delayed delivery. In both modules relevant data (including downloadable PDFs of an overview and/or the original manuscripts) will be available. All care providers in the participating centres will be expected to utilize this resource. Staffs who have omitted to use them will be prompted to do so. The final module will ‘test’ what has been learned and those who pass will be awarded a formal signed certificate of proficiency. The e-learning will be available to the providers at the time of the transition phase of the intervention. Seminars and meetings will complement these strategies.

Phase 3: the KT strategy for the study will be outlined and discussed. Participants will be asked to assess potential barriers, which can be minimised in future training interactions for Phase 4.

Phase 5: the use of the knowledge will be monitored and graded as monthly assessment during the intervention. Aspects regarding number of preterm births, whether all women for whom the intervention was indicated were treated and whether the information was used appropriately will be important points. If there is a suggestion that the intervention is not being performed when indicated or not used appropriately we will institute face-to-face seminars to identify and modify obstacles. The identification of specific practitioners who are accounting for the deficiencies we will meet with them for focussed determination of specific obstacles.

Phase 6: this phase will focus on clinical outcomes monitoring.

### Data management

All demographic and clinical data will be entered into a secure Internet based database designed and maintained by MedSciNetAB. This is the Global Pre-eclampsia Database which has been developed by CoLab (Global Pregnancy Collaboration) with MedSciNet and modified as appropriate for PREPARE. MedSciNet databases provide a secure and globally accessible data entry system that conforms to relevant FDA, NIH, and HL7 standards, guidelines, and recommendations (http://medscinet.com/projects.aspx). This data solution has been used for numerous clinical trials and studies globally, including several led by PIs of this project, and WHO studies in low to middle income countries. Data is held on software deployed on servers located in a data centre in Stockholm, operated in compliance with ISO27000 and SAS-70 standards and with 24 × 7 monitoring. Predefined reports are generated from an inventory, which logs sample deposition and removal.

Two research managers of the study will monitor data completion regularly and inform responsible researchers at each centre regarding problems to be addressed and corrected. All data must be completed up to 4 weeks after expected date to deliver.

Development of a biorrepository to test for unique pre-eclampsia features in Brazil, and for future mechanistic studies Additional file 2.

All women admitted with suspected or diagnosed pre-eclampsia will be invite to provide 20 mL of blood and 10 mL of urine. Therefore, plasma, serum, cells for DNA and urine will be stored in the facilities for long term sample storage (Biorepository). This biorrepository will be located at the Study Centre Laboratory, Medical School, Botucatu São Paulo State University, where -80 °C freezers with a nitrogen back-up system purchased for this purpose will be installed in the Laboratory for Clinical and Experimental Investigation with emergency power and alarms. In the event of freezer malfunction back-up freezers are available at this site for use during freezer repair. Informed consent will be requested for this purpose and will be taken by nurses that make part of the groups in each participant centre.

### Data safety and monitoring committee (DMC)

Monitoring of the accuracy and adequacy of data collection will be the responsibility of the Data Manager. He/she will investigate and wherever possible correct implausible entries and missing fields as they occur. Systematic problems will be referred to the Management Committee. A Data Monitoring Committee that will meet every four months will review the progress of the trial in terms of outcomes and results.

All responsible researchers by each centre have been instructed to report specific and important adverse outcomes involved with women participating in the trial. These specific adverse outcomes are: maternal death, fetal or neonatal death, eclampsia, HELLP syndrome, stroke and pulmonary edema requiring ventilation.

Rules for stopping the trial: It is possible for the intervention to result in inappropriate prolongation of pregnancy and serious events leading to adverse maternal or foetal/neonatal outcomes. The DMC will use the Haybittle-Peto rule, and stop the intervention if the *p*-value of the interim analysis is less than *P* < 0.001, and carry out a full interim analysis adjusting for baseline.

If these committees determine that this intervention is being used appropriately and increases adverse outcomes, then the trial will be stopped.

### Ethical consideration and trial registration

This study was approved by the national central ethical committee on research involving Human Subjects (CAAE: 53092916.4.2008.5411) and by each local ethical committee of the participating centres. The trial was registered at the ClinicalTrials.gov: NCT03073317.

The PREPARE Trial is hospital wide intervention, so all women admitted with suspected or diagnosed pre-eclampsia will be managed under local protocols during the baseline phase and under the PREPARE protocol during the intervention phase. Therefore, informed consent will be obtained for sample collection destined to be used in ancillary studies. All informed consent will be taken by the team involved in the project at each centre Additional file 1.

Important modifications necessary to protocol will be previously informed by the PI and all centres will be visited in order to clarify any changes.

### Statistical issues

#### Sample size

The primary aim is to test whether care targeted at preventing unnecessary delivery of women with pre-eclampsia will reduce the proportion of women delivered in the centres with preterm pre-eclampsia (deliveries with preterm pre-eclampsia/total deliveries). The power calculation depends on estimates of the total number of births, current pre-eclampsia prevalence and proportion with preterm deliveries from the seven centres (which have already agreed to participate). We estimate the mean number of infants born in each month per centre to be 330, and that of these ~ 5% will be born to women with pre-eclampsia. The preterm rate among those women with pre-eclampsia is approximately 36%. Therefore each month, there will be the potential to enter 17 women with pre-eclampsia, of whom approximately 6 would deliver prematurely, and outcome data will be available for approximately 700 deliveries of women with preterm pre-eclampsia. There is limited information on likely intracluster correlation (ICC) for this outcome in this setting and so we have explored sensitivity to a range of values.

Power calculations for stepped wedge cluster trials were as described in Hussy and Hughs [18]. Assuming that seven centres take part and allowing for a one month transition phase, and that in each centre there are approximately 17 cases of pre-eclampsia and 330 deliveries per month (with outcome data available for all deliveries), this study will have 89.6% power to detect a reduction in preterm deliveries associated with pre-eclampsia in the study centres from a population estimate of 1.5 to 1.0%, representing a 33% risk reduction, and 79.6% power to detect a reduction from 2.0 to 1.5% (25% risk reduction). Although the ICC is included in the power calculation, the design was found to be insensitive to the ICC and sensitivity analyses showed that these calculations were robust to larger magnitudes of ICCs.

### Data analysis

Hospital baseline characteristics of pregnancy outcomes to be collected throughout the data retrieval period will include numbers of women developing pre-eclampsia, women with preterm pre-eclampsia, gestational age at delivery of all hospital deliveries, and maternal and neonatal inpatient nights in women with pre-eclampsia. These baseline characteristics will be compared between exposure and non-exposure to the intervention and will be summarised by their means and standard deviations, medians and inter-quartile ranges, or numbers and percentages as appropriate. Centres will be classified as being exposed to the intervention one month after the centre was randomised to the intervention, and outcomes during the transition months will not be included.

The primary goal of the study is to test whether a care pathway targeted at preventing unnecessary delivery of women with pre-eclampsia will reduce the proportion of women delivered in the centres with preterm pre-eclampsia (deliveries with preterm pre-eclampsia/total deliveries). In statistical terms this null-hypothesis (no difference) can be tested using a mixed effects logistic regression model, with an indicator of whether the centre was exposed to the intervention as the dependent variable. Important independent variables to consider are the clustering effect (i.e. effect of centre), calendar time effect (since the intervention is sequentially rolled-out) and an indicator of intervention exposure for each centre at each time point; in additional to adjustment for other characteristics. Both individual and cluster level covariates to be included in the adjustment will be pre-specified and will include maternal age, parity, pre-existing chronic hypertension or other risk factors for prematurity. Null hypotheses and analyses for secondary outcomes take a similar form to that for the primary outcome, with appropriate link functions in the generalized linear mixed model. Summary treatment effect estimates will be reported (odds ratios or risk ratios) along with 95% CIs. These models will be fitted using population-averaged models using mixed effects methods in Stata version 14.2 or later (StataCorp, College Station, Texas).

The final trial dataset access will be limited to the authors of this study protocol.

Data will be disseminated through scientific meetings and peer-reviewed publications. Authorship of all publications will be shared among authors of this manuscript. Collaborators will be also listed in authorship as PREPARE research group.

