**Fig. 1 Fig1:**
[figure not shown]
Description of randomisation and implementation of the intervention for the Stepped Wedge design. There will be an initial four-month period of baseline data collection at hospitals, during which none of the centres will be exposed to the intervention. Subsequently, every four months, one centre will be randomised to the intervention. Four months prior to implementation, the centre will be engaged in a programme of intensive knowledge transfer, followed by one month of transition

Routine clinical data will be collected for the trial on all pregnant women with suspected or diagnosed pre-eclampsia that present to the participating centres between 20 + 0 and 36 + 6 weeks’ gestation.

In addition, they will be invited to sign the informed consent form, and provide additional samples for research purposes.

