### Outcome measures

#### Primary

Proportion of women delivered in the centres with preterm pre-eclampsia (deliveries with preterm pre-eclampsia/ total deliveries), where preterm is < 37 weeks’ gestation.

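### Dropping outcomes by the month in which they occur suits the delivery-based primary outcome, but for prolongation of pregnancy it selects on the outcome and biases the estimated gain in days

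*Protocol article*

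**What the plan says.** The rule is in the Data analysis section of the protocol article. It has two parts, joined in one sentence: "Centres will be classified as being exposed to the intervention one month after the centre was randomised to the intervention, and outcomes during the transition" period are left out. Exposure is thus a property of the centre in calendar time. The exclusion is worded by when the outcome happens: "outcomes during the transition months will not be included". The exposure term in the model is likewise "an indicator of intervention exposure for each centre at each time point". No sentence says which of a woman's dates, presentation or delivery, places her in a phase.

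The primary outcome is "Proportion of women delivered in the centres with preterm pre-eclampsia", with all deliveries as denominator. For the rest, the same section says "Null hypotheses and analyses for secondary outcomes take a similar form to that for the primary outcome", with a suitable link function and no separate phase rule. One of the secondary outcomes is "prolongation of pregnancy", whose starting point is not defined.

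Women enter when they present, at 20+0 to 36+6 weeks (Inclusion criteria), and the text below Fig. 1 confirms this for data collection: "Routine clinical data will be collected for the trial on all pregnant women with suspected or diagnosed pre-eclampsia that present to the participating centres". The Ethical consideration section says that care follows the phase in force. Nothing deals with women who present before a centre crosses over and deliver during or after its transition month.

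**The concern.** For a ratio of deliveries, the delivery is both the event and the unit, so dating everything by delivery is coherent. For prolongation, the delivery date is the presentation date plus the outcome. A rule that drops deliveries in a given month therefore drops women according to how long their pregnancy lasted. Of two women who present a week before crossover, the one who delivers in three days stays as a control and the one who delivers in three weeks is removed. A third who delivers after the transition month is either moved to the exposed phase or kept as control, depending on a date rule that is not stated.

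Prolongation is the direct measure of whether the recommendation to defer delivery changed practice. The stopping rules also name inappropriate prolongation as a safety worry. An estimate in days that moves with an unstated convention serves neither purpose.

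**Working it through.** **The plan's own figure.** The stated power concerns the primary outcome. Inputs from the Methods/design and Sample size sections: 7 centres, 32 months, 330 deliveries per centre-month, one transition month per centre. Assumed: two-sided alpha 0.05. With the Hussey-Hughes variance, fixed periods, each centre's transition month removed, control-rate variance and ICC 0.0005, power is 89.8% for 1.5% to 1.0% and 80.1% for 2.0% to 1.5%, against the stated 89.6% and 79.6%. The figures reproduce, and this point does not touch them.

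**How many control women are affected.** The documents give no interval from presentation to delivery. Assume it is exponential with mean m days and that women present evenly over time. Write L = 30.4 days for the transition month and q = exp(-L/m). With crossovers at months 4, 8, ..., 28, the control phases total 4 + 8 + ... + 28 = 112 months, or 112 x 30.4 = 3,405 days.

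- Share of control presenters who deliver in the transition month: 7m(1 - q)/3,405.
- Share who deliver later: 7mq/3,405.
- Mean interval of those in the transition month: 2m - Lq/(1 - q).
- Mean interval of those delivering later: 2m + L.

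| m | q | in transition month | mean interval | later | mean interval |
|---|---|---|---|---|---|
| 7 | 0.013 | 1.4% | 13.6 d | 0.02% | 44 d |
| 14 | 0.114 | 2.6% | 24.1 d | 0.3% | 58 d |
| 21 | 0.235 | 3.3% | 32.7 d | 1.0% | 72 d |

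Few women are lost, but they are the long pregnancies. At m = 14, removing both groups leaves controls with a mean of (14 - 0.0255 x 24.1 - 0.0033 x 58.4)/(1 - 0.0288) = 13.6 days.

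**Effect on the adjusted estimate.** Three rules were simulated on this layout, with centre and four-month-period effects in the model:

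- A: phase and exclusion both by delivery date.
- B: phase by presentation date, deliveries in the transition month dropped.
- C: phase and exclusion both by presentation date.

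First set: exponential intervals and a true 30% lengthening, with undelivered women changing care when the centre's exposure starts.

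| m | true gain | A | B | C | B with no true effect |
|---|---|---|---|---|---|
| 7 | 2.1 d | 1.9 | 2.4 | 2.1 | +0.3 |
| 14 | 4.2 d | 3.4 | 4.9 | 4.2 | +0.8 |
| 21 | 6.3 d | 4.4 | 7.2 | 6.1 | +1.1 |

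Rule A: 1.9/2.1, 3.4/4.2 and 4.4/6.3 are shortfalls of 10%, 19% and 30% (another run gave 4.6 in the last row, 27%). Rule B: 2.4/2.1, 4.9/4.2 and 7.2/6.3 are excesses of 14%, 17% and 14%, or 12-16% in one run before rounding.

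Second set: gamma intervals (the shape 1 results are shown for A and B), a true gain of 5 days, mean intervals of 7 / 14 / 21 / 28 days.

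- A: 4.3 / 3.6 / 3.2 / 2.7 days if women keep the care of their phase at presentation; 4.4 / 4.1 / 3.8 / 3.3 if they change care. With no true effect: -0.04 to +0.21 day.
- B: 5.3 / 5.7 / 6.2 / 6.3 days. With no true effect: +0.25 / +0.76 / +1.06 / +1.33.
- C: 4.74 to 5.11 days over all settings, including shape 2. With no true effect: -0.11 to +0.03.

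**Why the directions differ.** Under A with no effect, women delivering in any calendar month have the same mix of intervals once recruitment has settled, so the adjusted estimate is near zero. With a real effect, deliveries soon after exposure starts come from women who presented earlier or whose stay was short, and the gain is diluted. Under B only the end of the control phase loses its long pregnancies, so the controls look too short.

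**The case against.** The protocol classifies centres, not women, and says nothing about which of a woman's dates counts. A reader might infer that exposure status itself is keyed to the outcome date. The text does not say so; only the exclusion is worded that way. The condensed sentence on secondary outcomes may be meant to cover hypotheses and link functions alone, and an unseen analysis plan may set the dates for each outcome. This stands as a limit on the claim. It does not remove it, because the exclusion is stated, is tied to when the outcome occurs, and has no exception for prolongation.

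A reader might also infer that the bias always favours the intervention. It does not. Inflation needs phase by presentation combined with exclusion by delivery. If both follow delivery, the adjusted model understates a real gain and shows almost nothing under no effect. Selection then also acts at the start of the exposed phase, because women who present in the transition month are dropped if they deliver quickly and counted as exposed if they deliver later.

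A further tempting reading is that all secondary outcomes are damaged. Two of the three leading ones are ratios of deliveries, for which the delivery date is natural, and several perinatal outcomes have births as their denominator. Only prolongation was simulated. Maternal complications and stay follow the same logic if counted from presentation, but no figure supports a size for them.

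Finally, the bias is modest beside the sampling error. With an SD equal to the mean interval of 7/14/21 days, the standard error of the adjusted effect is about 0.9/1.9/2.8 days for the 750 women in the abstract, and about 0.4/0.8/1.3 days at 17 women per centre-month. The spurious 0.3/0.8/1.1 days under B are thus 0.3-0.4 standard errors in the first case and about 0.75-1.0 in the second. That argues for proportion, not for leaving an avoidable bias in place.

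**Conclusion.** The point holds for prolongation of pregnancy and in a limited form. As worded, the transition exclusion depends on the outcome being analysed. At assumed mean intervals of 7-21 days, a real gain is understated by roughly 10-30% if phase also follows delivery date. If phase follows presentation date, the gain is overstated by roughly 12-17%, and about 0.3-1.1 days appear where there is no effect. The percentages shift with the assumptions: in the second set, the shortfall under A reaches 37% at 21 days (3.16 of 5), and the excess under B runs from 6% at 7 days (5.31) to 25% at 21 days (6.23). Keying both rules to presentation recovers the true value closely.

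The sizes rest on an interval that the document does not give and on presentation as the start of prolongation, which is an inference. The primary outcome and its stated power are unaffected. The change should be made, but it does not threaten the trial's main conclusion.

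**What to change.** Keep the delivery date for the primary outcome and the other ratios of deliveries. For prolongation, and for any other outcome counted from presentation:

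- define the start as first presentation with suspected or confirmed pre-eclampsia;
- assign phase by that date, and exclude women who present in the transition month;
- follow every other woman to delivery and keep her outcome, whichever month it falls in;
- state that women undelivered at crossover are analysed in their phase at presentation.

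This changes wording only and should need no new data, since women are recorded from presentation. The cost is slight dilution from control women who become exposed after their centre's exposure starts: 0.2 day or less at mean intervals of 7-21 days in these simulations, and about 0.25 day at 28 days (4.74 against a true 5). The same woman may also count as control for prolongation and as exposed for the primary outcome. That is acceptable if the text says so.

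### The primary model is misstated: intervention exposure is named as the dependent variable and the primary outcome has no place in the model (a drafting error, corrected in one sentence)

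*Protocol article*

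**What the plan says.** The primary outcome, under Outcome measures, is the "Proportion of women delivered in the centres with preterm pre-eclampsia (deliveries with preterm pre-eclampsia/ total deliveries), where preterm is < 37 weeks’ gestation". The Sample size section powers the trial on that proportion, and the Data analysis section repeats it as the goal of the study.

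The Data analysis section then specifies the test as a "mixed effects logistic regression model, with an indicator of whether the centre was exposed to the intervention as the dependent variable". Its list of independent variables comprises the centre effect, a calendar time effect and "an indicator of intervention exposure for each centre at each time point", plus adjustment covariates that "will include maternal age, parity, pre-existing chronic hypertension or other risk factors for prematurity".

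On the remaining analyses it says "Null hypotheses and analyses for secondary outcomes take a similar form to that for the primary outcome", and adds in the same sentence that link functions are to suit the outcome. On reporting: "Summary treatment effect estimates will be reported (odds ratios or risk ratios) along with 95% CIs".

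**The concern.** The sentence that describes the primary test names the wrong response variable. Exposure stands on both sides of the model, and delivery with preterm pre-eclampsia stands on neither. This differs from a detail left to a fuller plan: the article makes a positive statement, and the statement is wrong. No other section gives a model in which the outcome is the response.

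What is at stake is the written definition of the primary analysis. A model without the outcome cannot produce the odds ratio or risk ratio that the same section promises, so a reader has to infer the confirmatory model.

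**Working it through.** **1. The plan's own figures, to see which model they imply.** Inputs from the article: 7 centres; one crossing every four months; 32 months of data, so 32/4 = 8 periods; 330 deliveries per centre-month; a one-month transition; reductions from 1.5% to 1.0% and from 2.0% to 1.5%. Two inputs are assumed: two-sided alpha 0.05 (inferred from the 95% CIs), and an ICC between 0 and 0.05, because no value is given.

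Method: Hussey and Hughes, power = Φ(|p1 − p2|/√V − 1.96). V is the generalised least squares variance of the exposure effect, with period effects, residual variance p(1 − p) per delivery and between-centre variance ICC/(1 − ICC) × p(1 − p).

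| Variant | 1.5% to 1.0% | 2.0% to 1.5% |
|---|---|---|
| Stated in the article | 89.6% | 79.6% |
| Transition month dropped, average-rate variance, ICC 0.01 | 91.5% | 80.6% |
| Same, ICC 0.05 | 91.4% | 80.4% |
| No month dropped, control-rate variance, ICC 0.01 | 88.9% | 78.9% |
| Transition month dropped, average-rate variance, ICC 0 | 99.4% | 96.6% |
| Every period cut to three months, average-rate variance, ICC 0.01 | 85.5% | 72.5% |

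The second, third and fourth rows lie within 2 points of the stated figures, so the figures are approximately reproduced if the ICC is about 0.01 or more. Each row treats the preterm pre-eclampsia proportion as the response and exposure as a predictor. The power calculation therefore already rests on the intended model and does not use the misstated one.

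**2. The model as written.** Number the centres k = 1 to 7 in crossing order and the periods t = 1 to 8. Centre k is exposed when t ≥ k + 1. There are 7 × 8 = 56 cells: 7 + 6 + 5 + 4 + 3 + 2 + 1 = 28 exposed and 28 unexposed. Dropping the transition month removes one month from each centre's first exposed period and leaves every cell with a single exposure value.

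Take the score s = 2(t − k) − 1. It is at least 1 in every exposed cell and at most −1 in every unexposed cell. It is a sum of a centre term and a period term, so a logistic model for exposure on centre and period can reproduce it. Multiplying s by an ever larger constant drives the likelihood towards 1, so no finite estimate exists. With exposure also listed as a predictor, separation is immediate, because the indicator predicts itself however centre and time are modelled.

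**3. A numerical illustration.** One data set was simulated with 7 × 32 − 7 = 217 centre-months of 330 deliveries, rates of 1.5% unexposed and 1.0% exposed, and no centre or time variation. The true odds ratio is (0.010/0.990)/(0.015/0.985) = 0.01010/0.01523 = 0.66. Centre and period were fitted as fixed effects.

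| Response | Result |
|---|---|
| Exposure (as written, exposure also a predictor) | Deviance about 3 × 10⁻⁹; exposure coefficient 51, SE about 53,000 |
| Preterm pre-eclampsia delivery | Odds ratio 0.56 (95% CI 0.44 to 0.71) |

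The second row is a single draw. It shows only that the effect is estimable on this layout once the outcome is the response.

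**The case against.** The strongest reply is that the paragraph corrects itself. The null hypothesis refers back to a goal stated in terms of the preterm pre-eclampsia proportion. The exposure indicator appears among the predictors, where it belongs. Treatment effects reported as odds ratios or risk ratios make sense only if the outcome is the response. The literal model cannot be fitted, so it cannot silently return a misleading answer. The wording is also permissive: it says how the hypothesis can be tested and which variables to consider, in an article that condenses a fuller plan.

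Most of this stands. It shows that the intended model can be recovered, but it does not make the sentence correct. The response variable was misstated rather than left for another document.

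Two stronger readings are tempting. One is that the trial has no valid primary analysis. The documents do not support it, because the goal, the outcome definition, the predictor list and the power calculation all point to a single feasible model. The other is that every secondary analysis carries the same error, because the form is said to be similar. The rest of that sentence lets the link function vary by outcome. That would serve no purpose if a binary exposure indicator were always the response, so the clause implies that each secondary outcome is the response in its own model.

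**Conclusion.** The Data analysis section misstates the primary model. Read literally, it has no finite fit in any of its 56 centre-periods' layout and gives no information on preterm pre-eclampsia delivery. This follows from the allocation schedule and from exposure standing on both sides; it needs no assumption about the ICC or event rates. In context it is a drafting error: the intended analysis can be inferred, and no sample size or power figure changes. It should still be corrected, because the primary analysis ought to be stated and not left to inference.

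**What to change.** Replace only the words that name the dependent variable. The response should be whether a delivery was a preterm (<37 weeks) delivery with pre-eclampsia, yes or no, among all deliveries. Add that the coefficient of the exposure indicator is the treatment effect.

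Leave centre, calendar time and the pre-specified covariates as already listed; the error gives no reason to drop covariates or to impose other modelling choices. For secondary outcomes, state that each outcome is the response in its own model with a suitable link, as the section already allows. One common binary form would not do, because prolongation of pregnancy and the lengths of stay are not binary.

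The cost is one corrected sentence and a short clarification, with no operational change and no effect on sample size or power.
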